#### Exclusion criteria

2.3.3

The exclusion criteria are as follows:

(1)with infertility caused by organic lesions of the reproductive system or female infertility;(2)with mixed antiglobulin reaction test for antisperm antibodies (+);(3)with abnormal sex hormone, abnormal seminal plasma biochemistry, or abnormal seminal plasma elastase;(4)with infertility caused by the unable to complete sexual intercourse, including but not limited to erectile dysfunction, ejaculatory disorder;(5)with reproductive system infection, such as chlamydia trachomatis or mycoplasma infection;(6)with a history of allergy to treatment drugs or allergic constitution;(7)use drugs affecting the experimental study within 3 months;(8)complicated with mental diseases, malignant tumor, or serious organic diseases;(9)participated in other clinical trials in the past 3 months.

### Sample size

2.4

Sample size was estimated based on the primary study results. Our previous pre-experiment have shown that the effective rate (*P*_1_) of the YSTL group (treatment group) is 79%, and the effective rate (*P*_2_) of the LOS group (control group) is 54%. The the following formula was used to estimate sample size: 

with a 5% significance level (*α*= 0.05, two-sided) and 90% power (*β*= 0.1), the final sample size has been set at a total of 160 patients (80 in each group), assuming a 15% dropout rate.

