### Primary outcome

4.1

The primary outcome in this trial is PR sperm rate (%) at baseline and the 4th, 8th, and 12th week after randomization.

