### Statistical analysis

4.5

Statistical Product and Service Solutions (SPSS21.0, International Business Machines Corp., Armonk, NY) software will be performed using for statistical analysis of data by professionals who will be blinded to the whole trial process. Analysis of the efficacy and safety will be based on the principle of intention-to-treat that all random participants will be analyzed. The missing value will be handled by the method of multiple imputations. Data will be presented as mean with standard deviation, median with range, or number with percentage, and different data types will be analyzed by appropriate methods. A repeated-measures multifactorial analysis will be used to analyze value changes of PR sperm rate, PR+NP sperm rate, total effective sperm count, and inner MMP in spermatozoa (See Table 1). The rest of the secondary outcomes will compare the different spouse pregnancy outcomes. Safety outcomes will be compared with the incidence of adverse events in two groups using the *χ*^2^ test. All the statistical tests will be conducted by bilateral difference tests, and if a *P* value is less than 0.05, the data difference will be considered statistically significant.

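### The stated 90% power is for a binary effective rate that is not an outcome of this trial, so it does not describe the primary comparison of PR sperm rate

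*Protocol article*

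**What the plan says.** All references are to the protocol article.

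- **Section 2.4 (Sample size)** rests on pilot results: "Our previous pre-experiment have shown that the effective rate" was 79% in the YSTL arm (P1) and 54% in the LOS arm (P2). The two-sided 5% level, 90% power and 160 patients (80 per arm) are attached to that contrast, "assuming a 15% dropout rate".
- **Section 4.1 (Primary outcome)** names a different quantity: "The primary outcome in this trial is PR sperm rate (%) at baseline and the 4th, 8th, and 12th week after randomization".
- **Sections 4.2 and 4.3** list PR+NP rate, total effective sperm count, sperm MMP, spouse pregnancy rate and the safety tests. An effective rate is not among them.
- **Section 4.5 (Statistical analysis)** treats PR as continuous: "A repeated-measures multifactorial analysis will be used to analyze value changes of PR sperm rate". The chi-square test is named only for adverse events, and no responder analysis is planned.

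The outcome lists in the Abstract and the Discussion agree with sections 4.1 to 4.3.

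**The concern.** A power figure describes one test of one quantity. Here that quantity is the proportion of patients classed as effective, while the primary question concerns a difference in PR. A reader who sees 90% in section 2.4 will naturally assign it to the primary outcome, and nothing in the article supports that.

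This matters because the comparator is an active drug, so the PR difference the trial was designed to detect is part of what a reader needs when weighing the result. The article gives neither that difference nor an SD for PR.

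The mismatch is between sections that are all on the page. An analysis plan could supply a definition of effective, but it could not make the 90% in section 2.4 refer to the analysis in section 4.5.

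**Working it through.** **1. Inputs from the documents.** P1 = 0.79, P2 = 0.54, alpha = 0.05 two-sided, power 0.90, dropout 15%, 80 per arm (section 2.4). Section 4.5 confirms the sidedness: "All the statistical tests will be conducted by bilateral difference tests".

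**2. Reproducing the plan's figure.** The formula itself is missing from the text at hand, which is not counted as an error. The unpooled two-proportion formula gives

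n = (1.960 + 1.282)² × [0.79 × 0.21 + 0.54 × 0.46] / 0.25² = 10.507 × 0.4143 / 0.0625 = 69.65 per arm.

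69.65 × 1.15 = 80.1, in line with the stated 80. The sizing is thus consistent with a comparison of two proportions.

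**3. Could 79% and 54% be something the trial does measure?**
- Mean PR: entry requires PR below 32% or PR+NP below 40% (section 2.3.1), and the figures are labelled as effective rates per group.
- Total effective sperm count: this is a count per patient, not a proportion of patients.
- Spouse pregnancy: the figures are not presented as pregnancy rates.

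None of these fits.

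**4. What 160 patients give for PR.** The documents hold no PR difference and no SD, so everything here is conditional. With 15% loss, 80 × 0.85 = 68 per arm. For two means at one visit, unadjusted, two-sided 5%:

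detectable difference at 90% power = (1.960 + 1.282) × √(2/68) = 0.556 SD.

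| Assumed SD of PR (points) | Difference with 90% power (points) |
|---|---|
| 8 | 4.4 |
| 10 | 5.6 |
| 12 | 6.7 |
| 15 | 8.3 |

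| Assumed true difference (SD) | Power at 68 per arm |
|---|---|
| 0.3 | 42% |
| 0.4 | 65% |
| 0.5 | 83% |
| 0.6 | 94% |

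With all 80 per arm contributing, the detectable difference is 0.51 SD.

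**5. Credit for baseline.** Adjusting for a baseline value with an assumed correlation of 0.5 multiplies the SD by √(1 − 0.5²) = 0.866. The detectable difference becomes 0.556 × 0.866 = 0.48 SD, and power at 0.4 SD rises from 65% to about 77%.

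**6. If effective were a single cut-off on PR.** Assume a normal PR distribution with equal SD in both arms. The implied shift is z(0.79) − z(0.54) = 0.706 SD. For 90% power that needs 2 × 10.507 / 0.706² = 42.2 per arm. At 68 per arm the power is about 98%.

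**The case against.** The strongest reply is that sizing on a dichotomised form of the primary variable is usually conservative. If effective was defined by a PR threshold, step 6 shows that the continuous analysis would have more than the stated power. This stands as far as it goes: the relation between the effective rate and PR is unknown, not absent. It does not rescue the 90%, because the article does not say that the rate is based on PR.

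The figures in step 4 also ignore the three post-baseline visits, and section 4.5 plans to use them. That is fair. They are illustrations of a simple comparison, and step 5 shows the direction in which a better use of the data moves them.

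An article may also leave the definition of a pilot endpoint to the full protocol. I agree, and the point does not depend on the missing definition.

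A reader might be tempted to infer more, and the documents do not support it:

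- **That the trial is underpowered for PR.** The powers in step 4 reflect the effects chosen for the table. They are not bounds on the trial's actual power, which cannot be computed from the article.
- **That a null result on PR could not be interpreted.** It would be read from the estimate and its confidence interval, which do not need the planned power.
- **That an effective rate will be constructed after the data are seen.** PR is named as primary and the secondary outcomes are listed, so a later responder rate would be visibly unlisted.

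**Conclusion.** The point holds as a mismatch within the article. The 90% power and the two-sided 5% level in section 2.4 belong to a 79% against 54% contrast that is not an outcome and has no planned test. They do not describe the repeated-measures comparison of PR.

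The arithmetic for the binary contrast reproduces, and there is no demonstrated shortage of patients. The conditional figure for PR is 90% power at 0.56 SD with 68 per arm. It assumes a single visit, no adjustment and 15% loss; the equivalents in points further assume an SD of 8 to 15. With baseline adjustment at a correlation of 0.5, it is about 0.48 SD.

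Severity: should-fix. The remedy alters what is claimed about the sample size, not the sample size, the outcomes or the data collected.

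**What to change.** Keep 160, and keep the record that it came from the effective-rate calculation, since that is how the number was chosen. In section 2.4:

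1. State that the 90% power applies only to the 79% against 54% contrast.
2. Add a power statement for the PR comparison. For example: with 68 evaluable patients per arm and a two-sided 5% level, a single-visit unadjusted comparison has 90% power for a difference of 0.56 SD, or about 0.48 SD with baseline adjustment if the correlation is 0.5.
3. Convert this to percentage points with the pilot SD of PR if the pilot recorded one. The article does not show that it did. Otherwise give the range as an assumption: 4.4 to 8.3 points unadjusted for SDs of 8 to 15.

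The cost is a few sentences and no extra patients. The downside is that the stated power may look less favourable once it is tied to PR.

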### Randomization and Blinding

2.5

Eligible participants who provide informed consent will be randomized at a 1:1 ratio into either YSTL group receiving a 12-week YSTL therapy or LOS group receiving the Levocarnitine Oral Solution therapy. Randomization will be performed based on a random list of numbers generated by SPSS21.0 software (International Business Machines Corp., Armonk, NY). An independent researcher will prepare the assignments in opaque envelopes containing an allocation sequence number and be responsible for the concealment of allocation sequence. Due to the specific nature of the intervention, it is not possible to blind the participants and personnel involved in conducting the trial. Outcome assessors, data managers, and statisticians will be unaware of the treatment allocations.

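### On its own inputs, 80 per arm less 15% dropout gives about 88% to 89% power, slightly short of the stated 90%

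*Protocol article*

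**What the plan says.** Section 2.4 (Sample size) of the protocol article takes its rates from a pre-experiment. The effective rate "of the YSTL group (treatment group) is 79" percent, and that "of the LOS group (control group) is 54" percent. The test level is given as "0.05, two-sided", with power of 90%. The result is that "the final sample size has been set at a total of 160 patients (80 in each group), assuming a 15% dropout rate".

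Section 2.5 (Randomization and Blinding) confirms equal allocation. The section does not give the number per arm before the dropout allowance, nor how the allowance was applied. The formula it refers to was lost when the text was extracted; that is not a fault of the plan.

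Section 4.5 (Statistical analysis) plans an intention-to-treat analysis of all randomised participants, with multiple imputation for missing values.

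**The concern.** When a size is stated to deliver 90% power with a 15% dropout allowance, the patients left after that loss should still give 90% power. Here 80 per arm becomes 68, which is fewer than the common two-sided formulas for two proportions require at 79% versus 54%.

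What is at stake is the accuracy of a planning figure that readers will quote. The validity of the trial is not in question.

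**Working it through.** **Inputs**, all from section 2.4 except the allocation ratio (section 2.5): p1 = 0.79, p2 = 0.54, difference d = 0.25; two-sided alpha 0.05 (z = 1.960); power 0.90 (z = 1.2816); dropout 15%; 80 per arm; 1:1 allocation.

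The variance terms are p1(1 − p1) = 0.1659 and p2(1 − p2) = 0.2484, sum 0.4143. The mean rate is 0.665, so 2 × 0.665 × 0.335 = 0.4456.

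**Step 1: can 80 be reproduced?** The formula is not visible, so several were tried.

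- Unpooled: n = (1.960 + 1.2816)² × 0.4143 / 0.25² = 10.507 × 0.4143 / 0.0625 = 69.65.
- 69.65 / 0.85 = 81.9, close to 80 but above it.
- 69.65 × 1.15 = 80.1, which matches 80 if rounded down.
- Pooled null variance: n = (1.960 × √0.4456 + 1.2816 × √0.4143)² / 0.0625 = 72.8. Then 72.8 / 0.85 = 85.7 and 72.8 × 1.15 = 83.7. Neither gives 80.

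The closest match is thus the unpooled formula with a factor of 1.15, but that route is inferred.

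**Step 2: evaluable patients needed against those left.** 80 × 0.85 = 68 per arm (136 in total).

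| Formula (two-sided) | Needed per arm | Divided by 0.85 |
|---|---|---|
| Unpooled variance | 69.65 (70) | 81.9 (82) |
| Arcsine | 72.4 (73) | 85.2 (86) |
| Pooled null variance | 72.8 (73) | 85.7 (86) |

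The required total is therefore 164 to 172. In the unpooled row, rounding 69.65 up to 70 before dividing gives 83 per arm (166 in total) instead of 82. A continuity correction would ask for more: 80.6 evaluable per arm, before any dropout.

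**Step 3: power at 68 per arm.**

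- Unpooled: Φ(0.25 / √(0.4143/68) − 1.960) = Φ(1.243) = 89.3%.
- Pooled: Φ((0.25 × √68 − 1.960 × √0.4456) / √0.4143) = Φ(1.170) = 87.9%.
- Exact enumeration of the Pearson chi-square test over all pairs of binomial outcomes: 88.5%.

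The shortfall from 90% is 0.7 to 2.1 points.

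**Step 4: what dropout would 160 tolerate at 90% power?** The pooled formula and the exact enumeration both first reach 90% at 73 per arm: 1 − 73/80 = 8.75%, about 9%. The unpooled formula needs 70: 1 − 70/80 = 12.5%.

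**Step 5: power with no information lost (80 per arm).** 93.5% unpooled, 92.5% pooled.

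**The case against.** The other side has a good case on most of the detail.

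- **Cause.** A reader might infer that the planners demonstrably multiplied by 1.15. The text does not support that. The formula and the pre-dropout number are not visible, and 80.1 would normally be rounded up to 81. A result of 81.9 trimmed to a round total of 160 is also plausible. The 1.15 route fits only the unpooled formula, where the shortfall is just 0.7 points. Under the pooled formula, where it is 2.1 points, the same slip would give 84.
- **Input precision.** The rates are printed as whole percentages. With 79.2% and 53.8%, which print the same, the unpooled calculation gives 67.3 / 0.85 = 79.2, and 80 per arm would suffice. Over the full rounding range (79.5% vs 53.5% to 78.5% vs 54.5%) it runs from about 75 to 89 per arm. This cuts both ways and does not establish 80, but it shows how narrow the gap is.
- **Analysis set.** Section 4.5 analyses everyone randomised, with multiple imputation, so 68 complete cases is the pessimistic bound. However, section 2.4 itself budgets for a 15% loss, and the article quantifies no information regained by imputation.
- **Relevance.** The effective rate is not among the outcomes listed in section 4. The primary outcome is the progressive motility rate, analysed by repeated measures, so the figure corrected here describes a comparison that is not the planned primary analysis.

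These points limit the size and certainty of the finding. They do not restore the stated figure: with the rates as printed, none of the two-sided formulas above reaches 90% at 68 per arm.

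**Conclusion.** The point holds as a small discrepancy in a stated planning figure. With 79% and 54% as printed, a two-sided 5% test and 15% of patients contributing nothing, 160 randomised patients give about 88% to 89% power. A claim of 90% with that dropout needs 164 to 172 in total, so 160 is 4 to 12 patients short.

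The result assumes that the printed rates are the planning inputs and that dropouts add no information. The cause is unconfirmed. It would be wrong to read this as a materially underpowered trial: the gap is at most 2.1 points under the uncorrected formulas and the exact Pearson calculation.

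**What to change.** Keep 160 and correct the sentence in section 2.4. Suggested content: 160 randomised, about 136 evaluable after 15% dropout, giving about 88% power for 79% versus 54% at the two-sided 5% level. Alternatively, keep 90% power and state that it allows for about 9% dropout. In either case give the formula's variance form, the number per arm before the allowance, and whether dropout was applied by dividing by 0.85 or by multiplying by 1.15.

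The cost is one or two sentences and a stated power about 1 to 2 points lower. No further recruitment and no change to the conduct of the trial is needed.

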### Randomization and Blinding

2.5

Eligible participants who provide informed consent will be randomized at a 1:1 ratio into either YSTL group receiving a 12-week YSTL therapy or LOS group receiving the Levocarnitine Oral Solution therapy. Randomization will be performed based on a random list of numbers generated by SPSS21.0 software (International Business Machines Corp., Armonk, NY). An independent researcher will prepare the assignments in opaque envelopes containing an allocation sequence number and be responsible for the concealment of allocation sequence. Due to the specific nature of the intervention, it is not possible to blind the participants and personnel involved in conducting the trial. Outcome assessors, data managers, and statisticians will be unaware of the treatment allocations.

## Interventions

3

### Basic interventions

3.1

Basic interventions will be given to the two groups including improvement of lifestyle to eliminate negative factors for physical and psychological, such as relief of tension, reduction of extra fat, avoid smoking or alcohol, appropriate of exercise, maintaining a comfortable mood.

### Drug intervention

3.2

#### YSTL group

3.2.1

YSTL consists of 12 g of Cuscuta chinensis Lam, 12 g of Epimedium brevicornu Maxim, 10 g of Rehmannia glutinosa, 12 g of Astragalus propinquus Schischkin,12 g of Salvia miltiorrhiza Bunge, and 10 g of Cyathula officinalis Kuan. Participants will be required to take the YSTL granules 2 times a day, 1 grid once a time, 0.5 hours after breakfast and dinner for 12 weeks. The granules produced by Sichuan Neo-green Pharmaceutical Technology Development Co., Ltd. (Sichuan, China) will be used in this study. The above-mentioned crude herbs will be extracted into granules, and the production process will meet the standard of Good Manufacturing Practice.

#### LOS group

3.2.2

Participants in this group will be required to take the Levocarnitine Oral Solution, 10 mL/piece, 3 times a day, 10 mL once a time, oral after meals. Levocarnitine Oral Solution will be manufactured by Northeast Pharmaceutical Group Shenyang No.1 Pharmaceutical Co., LTD. 12 weeks is one course of treatment and the participants will receive one course of medication. All drugs will be used should be the same lot number.

### Combined treatment regulations

3.3

During the study, it is forbidden to add other Chinese and western drugs or interventions (such as acupuncture, cupping, and massage) that may interfere with the trial. For participants with other existing conditions, if combined treatment cannot stop, the accompanying intervention should be recorded name, dosage, and the number of times in detail. If the disease progresses during the study, participants can withdraw from the study and use other treatment methods. The case will be treated as an excluded case, and patients will be required to complete the relevant examinations and assessments as much as possible.

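### Section 3.3 classes participants who withdraw on disease progression as excluded cases without defining the term; if that means excluded from analysis, it conflicts with the intention-to-treat rule in section 4.5

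*Protocol article*

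**What the plan says.** Section 3.3 (Combined treatment regulations) covers progression in two sentences. The first reads "If the disease progresses during the study, participants can withdraw from the study and use other treatment methods". The second opens with "The case will be treated as an excluded case" and goes on to ask that "patients will be required to complete the relevant examinations and assessments as much as possible".

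Section 4.5 (Statistical analysis) is the only place that sets the analysis population: "Analysis of the efficacy and safety will be based on the principle of intention-to-treat that all random participants will be analyzed". It adds: "The missing value will be handled by the method of multiple imputations".

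Section 2.5 (Randomization and Blinding) states that "it is not possible to blind the participants and personnel involved in conducting the trial", and also that "Outcome assessors, data managers, and statisticians will be unaware of the treatment allocations".

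No section says what an excluded case is excluded from, ties the term to a per-protocol set, or links it to section 4.5.

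**The concern.** Progression occurs after randomisation and is itself a bad outcome. Leaving such patients out of the comparison selects on treatment failure, and the remaining patients in each arm are no longer the groups that were randomised. Participants and treating staff know the allocation, so the readiness to call progression and change treatment could differ between arms. Blinded assessors, data managers and statisticians do not protect against this, because the selection happens before they see the data.

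At stake is who is counted in the primary comparison of progressive motility. The secondary outcomes and the adverse-event comparison are affected too, since 4.5 applies one population rule to both efficacy and safety. Two analysts working from this text could analyse different populations.

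**Working it through.** **1. The two rules side by side**

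| Meaning of excluded case | Section 3.3 | Section 4.5 | Compatible? |
|---|---|---|---|
| Left out of the analysis | progressors who withdraw are dropped | all randomised are analysed | No |
| Off study treatment only | progressors stop study treatment and assessments continue | all randomised are analysed | Yes |

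The text does not say which meaning applies. The conflict therefore depends on the first reading. The ambiguity exists under either.

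**2. The plan's own figure**

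Inputs from section 2.4: effective rates 79% (YSTL) and 54% (LOS), two-sided α = 0.05, power 90%, dropout 15%, total 160 (80 per arm). With the unpooled formula:

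n = (1.960 + 1.282)² × [0.79×0.21 + 0.54×0.46] / 0.25² = 10.507 × 0.4143 / 0.0625 = 69.65 per arm

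69.65 × 1.15 = 80.1 (81 per arm if rounded up). The stated 80 is reproduced to within one patient per arm. This only confirms the scale used below; the point does not rest on it.

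**3. Effect of exclusion on the effective-rate scale**

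Assumptions, not in the protocol: every excluded case would have been a failure, and 0 to 12 of 80 per arm are excluded. The upper end, 12/80 = 15%, equals the assumed dropout for all reasons.

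If x failures are removed from an arm of 80 with true rate p, the observed rate is 80p / (80 − x).

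(a) No true difference, 54% in both arms (80 × 0.54 = 43.2):

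| Excluded, arm A / arm B | Arm A | Arm B | Apparent difference (A − B) |
|---|---|---|---|
| equal numbers | same | same | 0 |
| 8 / 4 | 43.2/72 = 60.0% | 43.2/76 = 56.8% | 3.2 points |
| 12 / 4 | 43.2/68 = 63.5% | 56.8% | 6.7 points |
| 12 / 0 | 63.5% | 54.0% | 9.5 points |

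The arm that loses more failures gains. Swapping the arms reverses the sign.

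(b) True rates 79% (YSTL) and 54% (LOS), true difference 25.0 points (80 × 0.79 = 63.2):

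| Excluded, YSTL / LOS | YSTL | LOS | Apparent difference |
|---|---|---|---|
| 4 / 4 | 83.2% | 56.8% | 26.3 points |
| 8 / 8 | 87.8% | 60.0% | 27.8 points |
| 12 / 12 | 63.2/68 = 92.9% | 63.5% | 29.4 points |
| 4 / 12 | 83.2% | 63.5% | 19.6 points |

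Equal exclusions of share w divide the difference by (1 − w): 25.0/0.85 = 29.4. So equal numbers are harmless only when the true rates are equal, and unequal numbers can inflate or shrink the difference.

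**The case against.** The strongest reply is that there is no contradiction. The phrase stands in a section on concomitant treatment, not in the analysis section, and it does not mention the analysis. The same sentence asks for continued assessments, which makes little sense for patients who will not be analysed. Section 4.5 is explicit and states the right principle. This stands in part: a reader might infer that the two rules can never both be followed, and the document does not support that, because the term may mean only off study treatment. But the article does not say so, and the plain sense of excluded points the other way.

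A second reply is that multiple imputation covers these patients. It does not settle the matter, because imputation fills values for patients in the analysis set and does not restore patients classed as excluded. Conversely, a reader might infer that the planned imputation is itself wrong because it assumes progressors behave like those who stayed. The article names the method without its model, such detail commonly sits in an analysis plan that is not shown here, and a model using a progressor's observed weeks 4 and 8 could carry some of the worsening forward. No fault is claimed there.

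A third reply is that the illustration is not on the primary outcome. That is correct. Progressive motility is a percentage measured at each visit, and the article gives neither its standard deviation nor how far progressors fall below the others. The effective-rate scale is used because it is the only one for which the article supplies figures.

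**Conclusion.** The point holds in conditional form. An undefined term in 3.3 leaves open whether patients who withdraw on progression are analysed. On the literal reading it contradicts 4.5 and removes patients on a post-randomisation, outcome-related event decided by unblinded people.

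In the illustration the distortion runs from nothing to 9.5 points when there is no true difference. With a true 25.0 points, equal exclusions of up to 12 per arm inflate it to as much as 29.4. Both results assume that every excluded case is a failure and that at most 15% of an arm is excluded.

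A reader might infer that the rule favours YSTL, or that a specific bias can be expected. The document supports neither: there is no progression rate, and the bias would favour LOS if LOS lost sufficiently more failures (19.6 points instead of 25.0 in the 4 / 12 example). Nor is this a fully open-label trial: assessors, data managers and statisticians are blinded, although that does not prevent this selection.

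**What to change.** Reconcile the two sections by rewording 3.3 and making the link to 4.5 explicit:

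- Record these participants as having discontinued study treatment, and state that they remain in the intention-to-treat analysis of 4.5. Align the preceding sentence, which speaks of withdrawing from the study, so that stopping study treatment is kept distinct from ending follow-up.
- Include the assessments that 3.3 already requests in that analysis. State explicitly that values obtained after other treatment are used as observed in the primary analysis, so that the choice of a treatment-policy comparison is visible.
- Confine any exclusion of these cases to a secondary per-protocol or sensitivity set, defined in advance.

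Optionally, add a sensitivity analysis that imputes values still missing after progression as worse than missing-at-random.

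The cost is a few sentences. The 160 randomised are the 160 analysed, and no new data are requested. Section 2.1 says the trial is already running, so the wording should be settled before anyone can see which reading favours which arm. The clinical rule on who may withdraw, and when, is not at issue.
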